#### Primary objectives

To find out the time to recover after surgery following TLH, NDVH and TAH.To calculate the total cost per surgery from a societal perspective for TLH, NDVH and TAH.To compare the cost-effectiveness of TLH versus NDVH versus TAH.

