### Outcome measures

The primary outcome is time to recover following hysterectomy (earliest time to resume all or a combination of activities done prior to surgery; resumption of cooking, washing clothes, sexual activity and occupation). The secondary outcomes are operative time (skin to skin), postoperative hospital stay, anaesthesia time, complications (bladder injury, ureteric injury, bowel injury, convert to laparotomy, vault haematoma, blood transfusion, postoperative fever, skin wound infection, urinary tract infection, respiratory tract infection, deep vein thrombosis/pulmonary embolism, re-operation), postoperative pain and total pain medication per day per patient, QALYs, urinary, sexual and bowel function and total cost per surgery. The outcome measures are shown in Table 1.

**Table 1 Tab1:** Outcome measures and study instruments

Outcomes	Study instrument
Time to recover	Patient filled data sheet at 6 weeks
Operative time	Data sheet on operative period filled by research assistant.
Postoperative hospital stay	Postoperative data sheet filled by research assistant
Cost	Direct costs based on preoperative, operative, postoperative, 6-week and 6-month data sheets filled by research assistant Indirect costs based on preoperative, postoperative, 6-week and 6-month data sheets filled by patient
Complications	Data sheet on operative, postoperative, 6-weeks and 6-months period filled by research assistant
Anaesthesia time	Data sheet on operative period filled by research assistant
Pain scores and pain medication	Data sheet on postoperative period filled by research assistant
Blood loss/change in haematocrit	Data sheet on operative and postoperative period filled by research assistant
QALYs	Paper-based EQ-5D-3L (Sinhala/Tamil) [16]
Urinary function	ICIQ-FLUTS (Sinhala/Tamil) questionnaire [18, 19]
Vaginal and sexual function	ICIQ-VS (Sinhala/Tamil) questionnaire [20]
Bowel function	Bowel symptoms questionnaire [21]

*EQ-5D-3L* EuroQoL group questionnaire on health-related quality of life, *ICIQ-FLUTS* International Consultation on Incontinence modular Questionnaire on Female Lower Urinary Tract Symptoms, *ICIQ-VS* International Consultation on Incontinence modular Questionnaire on Vaginal Symptoms, *QALYs* Quality-adjusted life years

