### Randomization

Block randomization in multiples of three will be carried out at each study site by opening sealed envelopes containing computer-generated block randomization numbers, with block sizes of six and nine to ensure roughly equal numbers of patients in each arm at any point in the study. The patients and medical team will not be blinded to the intervention with only the statistician performing the analyses being blinded.

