### Data analysis

All randomized patients will be included in the analyses. A single principal analysis will be done comparing the three arms (TAH, NDVH and TLH) 12 months after the last woman has had her operation. The fact that the trial will be conducted at two centres will be taken into account during data analysis.

A Kaplan–Meier survival analysis will be done for the primary outcome which is time to recover following hysterectomy. The end-point is the actual time to recover. It will be assessed and documented at the 6-week clinic visit. Patients who have not recovered by 6-weeks will be followed-up beyond 6-weeks to detect complications and the actual time to recover. Post hoc pairwise analysis between TAH, NDVH and TLH will be done using COX regression.

Other outcomes that need follow-up; QALYs, urinary, vaginal and bowel functions will also be analysed using Kaplan Meier survival analyses. The end point for QALYs is 6-months while for urinary, vaginal and sexual function it is 1-year. Patients who do not complete follow-up in these secondary outcomes will be right censored up to their respective end-points. Post hoc pairwise analysis between TAH, NDVH and TLH will be done using COX regression. The other outcomes; operative time, anaesthesia time, postoperative hospital stay, cost, pain scores and blood loss will be analysed using Kruskal-Wallis test with post hoc comparisons. The complications will be described for each category. A fully specified Statistical Analysis Plan will be provided before opening the database.

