### Economic evaluation

The economic evaluation will take societal perspective and will include direct costs related to utilization of healthcare resources in the hospital and indirect costs which are borne by the patient. A micro-costing approach will be adopted to calculate utilization of hospital resources from the time of presentation to the gynaecology clinic up to six months after surgery. Incremental cost-effectiveness ratios (ICER) will be obtained by calculating the incremental costs divided by the incremental effects (time to recover and QALYs gained) for the intervention groups (NDVH and TLH) over the standard care (TAH) group.

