### Resource use and costs

Direct costs would include surgical costs, clinic costs, investigation costs and care during hospital stay. Surgical costs will consider staff cost, equipment cost, anaesthetic costs and cost of basic utilities; water, electricity and building cost. Clinic costs will entail staff cost, equipment cost and cost of basic utilities for clinics during the preoperative and postoperative period. Investigation costs will include laboratory and imaging costs for preoperative period and postoperative period. Information on routine investigations; full blood count, blood urea, serum electrolytes, urine full report, ECG, chest X-ray, transvaginal ultrasound scan (TVS) and any other additional investigation would be collected from clinic and in-ward medical records by the data collector on to a data sheet. The cost of hospital stay will include staff costs, cost of medicines and basic utilities. Information on healthcare costs were obtained from the medical supplies division of the Ministry of Health, Sri Lanka. Information on labour costs and basic utilities were obtained separately for each centre. Indirect costs will consider costs of additional investigations and medicines paid for by the patient, travel costs to and from the hospital/clinic, cost for carers and productivity losses for the patients and families and will be obtained by patient-filled questionnaires.

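### Cost is compared between arms only by an unstratified rank test, while the cost objectives and the ICER need a difference in mean cost, preferably adjusted for centre

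*Protocol article*

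**What the plan says.** Primary objectives includes "To calculate the total cost per surgery from a societal perspective for TLH, NDVH and TAH" and "To compare the cost-effectiveness of TLH versus NDVH versus TAH". Outcome measures places total cost among the secondary outcomes, at the end of the list: "QALYs, urinary, sexual and bowel function and total cost per surgery".

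Data analysis fixes the method for a group of outcomes that includes cost: "operative time, anaesthesia time, postoperative hospital stay, cost, pain scores and blood loss will be analysed using Kruskal-Wallis test with post hoc comparisons". The same section states: "The fact that the trial will be conducted at two centres will be taken into account during data analysis". It does not say how, and it announces a full statistical analysis plan to follow before the database is opened.

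Economic evaluation obtains the ICER, for NDVH and for TLH over TAH, by "calculating the incremental costs divided by the incremental effects (time to recover and QALYs gained"). No mean-based between-arm comparison of cost is named there or under Resource use and costs.

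Two facts bear on centre. Randomization says: "Block randomization in multiples of three will be carried out at each study site". Resource use and costs says: "Information on labour costs and basic utilities were obtained separately for each centre".

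**The concern.** A payer's budget and an ICER both depend on the arithmetic mean cost per patient, because mean cost multiplied by the number of patients gives total spending. A rank test answers another question: whether costs in one arm tend to be higher or lower than in another. It gives a p-value but no cost difference in money and no interval for one. It is also insensitive to a few very expensive patients, such as those with a re-operation, a readmission or a conversion to laparotomy, who can dominate a mean.

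The trial could therefore report a cost p-value and an incremental cost that seem to tell different stories. A real excess in mean cost could go with a non-significant test, or a significant test could go with an incremental cost near zero. The cost objectives would have no stated measure of uncertainty for the quantity they concern.

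The named test also ignores centre. Labour and utility costs were obtained separately for each centre, so cost can differ between the hospitals by construction. That variation stays in the error of an unstratified test.

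**Working it through.** **Inputs from the document.** There are 49 women per arm (Sample size calculation), three arms, two centres and randomisation blocked within centre. The 49 is based on time to recover, not on cost. It reproduces with a 7-day difference, SDs 9.5 and 8.5, two-sided α = 0.01 and 80% power:

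n = (9.5² + 8.5²)(2.576 + 0.842)² / 7² = 162.5 × 11.68 / 49 = 38.7, so 39; 39 / 0.8 = 48.75, so 49 per arm.

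The document gives no mean, SD or shape for cost and no numbers per centre. Everything below rests on assumed distributions and shows direction, not predicted size. All tests are at 0.05.

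**Step 1: how ranks and means separate.** For a log-normal cost with log-mean μ and log-SD σ, the median is exp(μ) and the mean is exp(μ + σ²/2). If two arms have the same median but different σ, the ratio of their means is exp((σ₁² − σ₂²)/2).

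- σ = 0.8 versus 0.4: exp((0.64 − 0.16)/2) = exp(0.24) = 1.27, a mean 27% higher.
- σ = 0.6 versus 0.3: exp((0.36 − 0.09)/2) = exp(0.135) = 1.14, a mean 14% higher.

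If the means are equal instead, the medians must differ. At 0.8 versus 0.4 the ratio of medians is exp(−0.24) = 0.79.

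**Step 2: simulated rejection rates, 49 per arm, one arm with the larger spread.**

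| Scenario | True mean difference | Kruskal-Wallis | Welch ANOVA (means) |
|---|---|---|---|
| Equal medians, log-SD 0.8 vs 0.4 | +27% | about 5% | about 18-19% |
| Equal medians, log-SD 0.6 vs 0.3 | +14% | about 5% | 15% |
| Equal means, log-SD 0.8 vs 0.4 | 0 | about 43% | not tabulated |

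In the first two rows Kruskal-Wallis stays near its null rate although mean cost differs. In the third it often rejects although the true incremental cost is zero. Welch ANOVA is the fair comparator because, like Kruskal-Wallis, it is a three-arm omnibus test. A single unadjusted pairwise Welch test gives about 27% in the first row, and setting that against an omnibus test would overstate the gap.

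**Step 3: a scenario favourable to ranks.** With a common log-SD and one arm's mean 27% higher, Kruskal-Wallis rejects in 86%, 49% and 30% of trials at log-SD 0.4, 0.6 and 0.8. A single pairwise Welch test rejects in 82%, 43% and 24%. When spread is equal the rank test is not inferior.

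**Step 4: centre.** Assumptions: normal outcome, 102 and 45 patients in the two centres, arms balanced within centre, and an effect of 0.6 SD in one arm.

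| Shift between centres (SD) | Power, plain Kruskal-Wallis | Power, centre-stratified rank test | Type I error, plain Kruskal-Wallis |
|---|---|---|---|
| 0 | 85% | 85% | 4.7% |
| 1 | 76% | 83% | 3.6% |
| 2 | 52% | 84% | 0.5% |
| 3 | 29% | 85% | 0.05% |

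Ignoring centre makes the test conservative and loses power. It does not produce false positives, because arms are balanced within centre.

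**The case against.** **The ICER is not computed from Kruskal-Wallis.** Economic evaluation is a separate section, and incremental cost there is by implication a difference in means. One of the two cost objectives is to calculate total cost, which is estimation, and total cost is a secondary outcome. A reader might infer that the plan would calculate the ICER wrongly or leave mean cost unestimated; the text does not support that. What remains is narrower: the only between-arm comparison named for cost does not address the ICER's numerator.

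**The promised analysis plan may settle this.** Bootstrap intervals, model links and centre adjustment are commonly left to such a plan, and their absence here is no fault. But the article does not leave the cost test open. It names one, and a later plan would either inherit the mismatch or have to depart from the published method.

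**Centre.** A reader might infer that the section contradicts itself, or that a rank analysis cannot allow for centre. Neither follows. The promise does not say how centre will be handled, and a centre-stratified rank test would honour it. What stands is that the test as named has no centre term, at a cost in precision only. Stratifying would not cure the mismatch between ranks and means.

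**The illustration is chosen against ranks.** Equal medians with doubled log-SD in one arm is an unfavourable case, and with equal spread Kruskal-Wallis does at least as well. This objection stands as to size. Unequal spread is nonetheless plausible: costs run to six months, and conversion to laparotomy can occur only at TLH or NDVH.

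**The other outcomes.** For operative time, anaesthesia time, stay, pain and blood loss a rank test is conventional and valid. Replacing it with regression would be preference.

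**Conclusion.** The concern holds in limited form. Kruskal-Wallis is the only between-arm comparison named for cost, and it does not target the mean difference that the cost objectives and the ICER need. It is not invalid as a comparison of distributions; the fault is that no mean-based comparison with an interval stands beside it.

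The size cannot be fixed from the document. If spread differs between arms as assumed (log-SD 0.8 versus 0.4), the test can miss a 27% excess in mean cost (about 5% rejection) or reject in about 43% of trials when mean costs are equal. If spread is equal, the choice of test does little harm and ranks may have somewhat more power. The point of principle does not depend on these figures: a rank test supplies no difference in mean cost and no interval.

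The centre point is a secondary improvement. Its size depends on an unknown difference between the hospitals (at an assumed 2 SD shift, power falls from 85% to 52%), and it concerns precision, not bias. The plan should be changed, but nothing here undermines the design, the sample size or the primary outcome.

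**What to change.** In Data analysis, take cost out of the Kruskal-Wallis list and state that it will be compared as the difference in arithmetic mean cost, NDVH versus TAH and TLH versus TAH, adjusted for centre. Use either linear regression with non-parametric bootstrap confidence intervals resampled within centre, or a generalised linear model (for example gamma) with arm and centre. Where the bootstrap is used, take the intervals from the same resamples as the ICER, so that the cost comparison and the ICER numerator concern one quantity. A rank test on cost may stay as supportive.

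For the other listed outcomes the rank test may stay, in centre-stratified form, for example van Elteren for the pairwise contrasts.

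The change is to analysis wording only and needs no new data or patients. It should be made before the database is opened. The price is slightly more analysis work and, where spread is equal across arms, a mean-based comparison with somewhat less power than ranks.

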### Economic evaluation

The economic evaluation will take societal perspective and will include direct costs related to utilization of healthcare resources in the hospital and indirect costs which are borne by the patient. A micro-costing approach will be adopted to calculate utilization of hospital resources from the time of presentation to the gynaecology clinic up to six months after surgery. Incremental cost-effectiveness ratios (ICER) will be obtained by calculating the incremental costs divided by the incremental effects (time to recover and QALYs gained) for the intervention groups (NDVH and TLH) over the standard care (TAH) group.

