### Patient selection and data collection

Eligible patients will be identified, counselled and enrolled by gynaecologists at each study centre. Before entry into the study the gynaecologist will explain to a potential patient the aims, methods, reasonably anticipated benefits and potential hazards of the study. Patient information sheets will be distributed to eligible patients and a research assistant will be available for a more detailed explanation. They will also explain to patients the potential benefit of extended long-term follow-up that would otherwise not be available and other intended benefits to the healthcare system as well as the country by participation in this research. After sufficient information, informed written consent will be obtained. Research assistants will assign enrolled participants to have either a TLH, NDVH or a TAH (Fig. 1). Patients who decline participation in the study will have standard treatment (TAH).

A preoperative questionnaire on general information, quality of life, pelvic organ function (urinary, vaginal and sexual and bowel function) and costs incurred up to surgery would be filled in by the patient while another on relevant medical information would be filled by a research assistant a day prior to surgery. Standard techniques of TLH, TAH and NDVH would be followed [15, 16]. The decision to convert to laparotomy at TLH or NDVH would be at the discretion of the primary surgeon.

Data on operative time, complications, instruments and medications used and staff allocation during surgery will be entered into a data collection sheet immediately after surgery. During the postoperative period the following information will be collected by a research assistant using a datasheet; complications, pain scores and analgesic medication and investigations. A patient-filled questionnaire will obtain costs incurred by the patient due to hospital admission. The health utility scores based on paper-based EuroQoL group health-related quality of life (EQ-5D-3L) questionnaires will be estimated on day 2 and 1 week post-surgery. (A self-addressed stamped envelope along with an EQ-5D-3L form will be provided to the patient on discharge with instructions to mail the 1-week assessment).

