### Description of study instruments

The validated paper-based Sinhala and Tamil EQ-5D-3L questionnaire will be used to obtain health utility scores. The EQ-5D-3L is a generic multi-attribute utility system, which assess health-related quality of life on five dimensions (mobility, self-care, usual activities, pain/discomfort, anxiety/depression) [17]. Based on the responses a woman will be placed in to one of 243 (3^5^) mutually exclusive health states, and a value for each of these has previously been estimated with ‘0’ being equivalent to dead and ‘1’ being equivalent to perfect health on a utility scale based on interviews. EQ-5D 3L questionnaires will be administered 1 day preoperatively and on postoperative day 2, 1 week, 6 weeks, 3 months and 6 months postoperatively. Each woman’s QALYs will be calculated using the utility score and the time spent on the particular health state. A utility value table specific to Sri Lanka will be used to calculate QALYs [18].

Urinary and sexual function will be assessed by the validated Sinhala and Tamil translations of International Consultation on Incontinence Modular Questionnaire on Female Urinary Tract Symptoms (ICIQ-FLUTS) and Incontinence Modular Questionnaire on Vaginal Symptoms ICIQ-VS which were obtained from the International Consultation on Incontinence (ICI) [19–21]. Bowel symptoms will be assessed by a questionnaire based on a study done by Tharkar et al. [22]. These questionnaires will be used preoperatively, 6 months and up to 1 year post-hysterectomy to detect changes in pelvic organ function.

Postoperative pain evaluation will be done using numeric pain rating scale (NRS) [23], asking the patient to indicate the intensity of current, best, and worst pain levels over the past 24 hours on a scale of 0 (no pain) to 10 (worst pain imaginable). The average of the three ratings; average, best, and worst will be used to represent the patient’s level of pain over the previous 24 hours. To allow direct comparison of pain medication a modified World Federation of Societies of Anaesthesiologists (WFSA) analgesic ladder will be used [24].

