### Local organisation in centres

Each centre will have a lead gynaecologist who will be the point of contact for that centre whose responsibilities will be: to establish the study locally, obtaining the required regulatory approval; to appoint and train a local research assistant; to inform all relevant local staff about the study (e.g. other consultant gynaecologists, junior medical staff, research assistants and ward staff); take responsibility for complications of the study locally; and notify the study centre of any unexpected complications due to the study. Fortnightly meetings involving gynaecologists, research assistants, junior medical staff and paramedical staff will be held at each local centre. The involved gynaecologists will identify eligible patients, explain the different surgery options to them, and ensure that study documentation has been provided and that informed consent has been obtained.

Each centre will have a local research assistant to organise recruitment of patients to the study. The responsibilities of the research assistant will be to: ensure that each participating patient has received the patient information leaflet and has given informed written consent, ensure that each participant has received all self-administered questionnaires, collect all relevant medical data on to the data sheet, keep a log of all eligible women and their recruitment status, maintain a register of all recruited patients, contact participants at relevant assessment points to obtain required data (at 1 week, 6 weeks, 3 months, 6 months and 1 year), systematic filing of study documents, data entry on to the computer database, notify the local lead gynaecologist of any problem or complication and inform local staff of progress of the study. In order to improve recruitment, research assistants will identify any eligible women in the ward who may have been missed at the gynaecology clinic.

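### The ICER counts hospital costs from before randomisation, which adds avoidable random error to the incremental cost but does not bias it

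*Protocol article*

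**What the plan says.** The Economic evaluation section sets the hospital-cost window: a micro-costing approach will "calculate utilization of hospital resources from the time of presentation to the gynaecology clinic up to six months after surgery". The Methods part of the Abstract gives the same window for direct costs. ICERs are then formed for NDVH and TLH, each against TAH, by dividing incremental cost by the incremental effect (time to recover, and QALYs).

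Allocation comes later than presentation. Under Patient selection and data collection, "Eligible patients will be identified, counselled and enrolled by gynaecologists at each study centre", and after written consent "Research assistants will assign enrolled participants to have either a TLH, NDVH or a TAH". Local organisation in centres adds that "research assistants will identify any eligible women in the ward who may have been missed at the gynaecology clinic", so some women may be enrolled only after admission. The interval from randomisation to surgery is not stated.

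Resource use and costs includes preoperative clinic and investigation costs. Patient-borne costs come partly from the preoperative form, on which "costs incurred up to surgery would be filled in by the patient". Table 1 likewise has "Indirect costs based on preoperative, postoperative, 6-week and 6-month data sheets filled by patient". No start date is given for patient-borne costs.

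The effects start later. Time to recover is counted from the operation, and "EQ-5D 3L questionnaires will be administered 1 day preoperatively" and then up to 6 months.

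Two of the three primary objectives depend on cost: total cost per surgery for each route, and the comparison of cost-effectiveness.

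**The concern.** A randomised comparison starts at randomisation. Clinic visits and investigations already completed by then cannot depend on the arm a woman later draws. Including them in the incremental cost adds a quantity whose true difference between arms is zero but whose observed difference is not. It also varies between women for reasons unrelated to the operation, such as how long they were under the clinic before enrolment.

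At stake is the precision of the ICER numerator, in a trial sized for time to recover and not for cost. The article does not say that this component will be removed or adjusted for. The only cost test it names, Kruskal-Wallis with post hoc comparisons (Data analysis), takes no covariate.

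**Working it through.** **Inputs from the article.** 49 women per arm; 20% loss to follow-up; two-sided type 1 error 0.01; power 80%; difference 7 days; SD 9.5 (TAH) and 8.5 (VH) (Sample size calculation). No mean or SD is given for any cost.

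**The plan's own figure.** The pooled variance for TAH and VH is (9.5² + 8.5²)/2 = 81.25, so the SD is 9.01. Then n = 2 × (2.576 + 0.842)² × 81.25 / 7² = 38.7, rounded up to 39 per arm. Allowing for loss, 39/0.8 = 48.75, rounded up to 49 per arm and 147 in total. This matches, so 49 randomised and 39 analysed per arm are used below.

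**Chance imbalance.** The standard error of the difference between two arms in mean pre-randomisation cost is SD_pre × √(2/n).
- n = 49: √(2/49) = 0.202 SD_pre; 95% range ±1.96 × 0.202 = ±0.40 SD_pre.
- n = 39: √(2/39) = 0.226 SD_pre; 95% range ±0.44 SD_pre.

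**Effect on the incremental cost.** Let k = SD(pre-randomisation cost)/SD(later cost) and ρ be their correlation. Both are assumptions. Including the pre-randomisation part multiplies the standard error by √(1 + k² + 2ρk).

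| k | Rise in SE, ρ = 0 | Rise in SE, ρ = 0.3 |
|---|---|---|
| 0.05 | 0.1% | 1.6% |
| 0.10 | 0.5% | 3.4% |
| 0.25 | 3.1% | 10.1% |
| 0.50 | 11.8% | 24.5% |
| 1.00 | 41.4% | 61.2% |

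For example, at k = 0.25: √(1 + 0.0625) = 1.031 with ρ = 0, and √(1 + 0.0625 + 0.15) = 1.101 with ρ = 0.3.

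**Check for bias.** In 20,000 simulated two-arm comparisons with 49 per arm, a true incremental cost of 0.50 SD of later cost, k = 0.25 and no correlation, the mean estimate was 0.498 without the pre-randomisation cost and 0.497 with it. The standard error rose from 0.202 to 0.209, about 3%. The expected difference does not move; only its precision does.

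**The case against.** Four arguments can be made for leaving the window alone.

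- **The loss may be trivial.** The preoperative hospital items in Resource use and costs are clinic running costs and a set of investigations described as routine, which may vary little between women. Later costs include theatre, anaesthesia, hospital stay and complications. That points to a small k, and at k = 0.25 or below the loss is about 3% or less without correlation. This stands as a plausible reading, but the article gives no figures to confirm it. The same section also allows for additional investigations.
- **The long window has a purpose.** Total cost per surgery is a primary objective in its own right, and preoperative costs belong in it. This stands, and it is why the full window should be kept for that objective.
- **The analysis plan can deal with it.** The article promises a full plan before the database is opened, and that plan is not shown. It could subtract or adjust for pre-randomisation cost. However, the article does not leave the window open: it states it in two places, so a plan starting at randomisation would need to say that it departs from it.
- **Not all preoperative cost is noise.** Costs between randomisation and surgery can depend on the arm. This stands. The split belongs at randomisation, not at surgery.

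A reader might go further and infer that the ICER is biased, or that its sign is in danger. The documents do not support this: the component cancels in expectation, and the interval around the cost difference already includes its variance. Nor do they support the view that productivity losses and other patient-borne costs are counted from first presentation. The stated window concerns hospital resources, and the patient form gives no start date.

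**Conclusion.** The point holds as one of precision. The stated window brings pre-randomisation hospital costs into the ICER numerator, where they can contribute only random error. The expected incremental cost is unchanged.

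The size cannot be fixed from the article. Without correlation, the standard error rises by 0.5% at k = 0.1, 3% at 0.25, 12% at 0.5 and 41% at 1. Quoting only the upper values, which correspond to losing 20% and 50% of the sample (1 − 1/(1 + k²)), would overstate the case, because nothing in the article supports a k that high.

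The conclusion rests on these assumptions:
- Cancellation in expectation requires that all randomised women are analysed. The Compliance issues and Data analysis sections differ on women who exit before surgery, which is a separate matter.
- The rise in standard error requires that ρ is not strongly negative. If ρ is below −k/2, then k² + 2ρk is below zero and the full window would be the less variable. This could occur if the same work-up falls before allocation in some women and after it in others.
- The different starting points of costs and effects are not in themselves the fault. Costs counted from randomisation would still start earlier than time to recover. The relevant boundary is randomisation.

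**What to change.** In the Economic evaluation section and the Abstract, or in the analysis plan with a note of the change:

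1. For the ICERs, count costs from randomisation to 6 months after surgery, including those between randomisation and surgery.
2. Where patient-reported preoperative costs cannot be split at the randomisation date, report the ICERs with and without them as a sensitivity analysis.
3. Keep the window from clinic presentation for the descriptive total cost per surgery. Setting the two totals side by side will also show whether the choice of window matters.

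The cost is a little more analysis work. Investigations are taken from clinic and ward medical records, so hospital items should be the easier ones to date. Patient-reported costs are harder: the form is completed the day before surgery, the article does not say that its entries are dated, and the first woman was randomised on 1 August 2016. Some totals already collected may not be separable, which is the reason for step 2. The sample size and the other outcomes are not affected.
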